### Definitions

Complications will be defined as follows:

Hematoma: A blood collection at the regional anesthesia site requiring medical and/or surgical intervention.Pneumothorax: The presence of an air crescent consistent with pneumothorax on the same side as the regional anesthesia, confirmed by ultrasound, chest X-ray, or chest CT scan.LAST: Any electrocardiographic, hemodynamic, and/or neurological alteration occurring after regional anesthesia, attributable to systemic absorption of local anesthetic and requiring treatment (e.g., lipid emulsion administration).Nerve injury: The onset of dysesthesia, anesthesia, or prolonged motor deficit not explained by the pharmacokinetics of the anesthetic used, within the distribution area consistent with the performed block.

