### Study design and objectives

This protocol has been prepared with the support of the SPIRIT checklist (see S1 File). The NEURAL study, promoted by the Italian Society of Anesthesia, Analgesia and Critical Care (SIAARTI), is a multicenter, prospective observational study designed to investigate the prevalence of complications associated with regional anesthesia of the upper limb, lower limb, and fascial plane blocks.

The primary objective of the NEURAL study is to determine the overall incidence of complications following regional anesthesia, expressed as a composite outcome. This composite outcome will include nerve injury, hematoma, pneumothorax, and LAST, calculated as the total number of complication events divided by the total number of procedures.

The secondary objectives are to determine the incidence of each individual complication (nerve injury, hematoma, pneumothorax, and LAST for each type of regional anesthesia technique. These include upper limb blocks, lower limb blocks, and fascial plane blocks (Table 1), with outcomes calculated as the number of events relative to the total number of procedures performed. In addition, the study seeks to identify risk factors associated with complications following upper limb regional anesthesia, lower limb regional anesthesia, and fascial plane blocks, thereby contributing to a more precise understanding of patient- and procedure-related variables influencing safety in regional anesthesia as described in the relevant paragraph below..

**Table 1 pone.0348493.t001:** Fascial plane regional anesthesia: The most recent nomenclature of the European Society of Regional Anaesthesia (ESRA) [7] will be used. The following blocks will be considered.

Upper limb blocks	Lower limb blocks	Fascial blocks

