Interscalene BP block Superior trunk block Supraclavicular BP block InfraclavicularBP block Infraclavicular BP block (coracoid approach) Infraclavicular BP block (retroclavicular approach) Infraclavicular BP block (costoclavicular approach) Suprascapular nerve block (anterior approach) Suprascapular nerve block (posterior approach) Axillary BP block Superficial cervical plexus block Intermediate cervical plexus block Deep cervical plexus block.	Lumbar plexus block Sacral plexus block Fascia iliaca block (suprainguinal approach) Fascia iliaca block (infrainguinal approach) Adductor canal block PENG block Femoral nerve block Femoral triangle block Sciatic nerve block (anterior approach) Sciatic nerve block (transgluteal approach) Sciatic nerve block (infragluteal approach) Sciatic nerve block at the popliteal fossa Nerve to vastus medialis block Genicular nerves block IPACK Common peroneal nerve block Ankle block Pudendal nerve block.	Rectus sheath block Ilioinguinal iliohypogastric nerves block TA block Midaxillary TAP block Subcostal transversus abdominis plane block ESP block Deep SAP block Superficial SAP block TFP block Rhomboid intercostal plane block Retrolaminar block Anterior QLB Lateral QLB Posterior QLB Paravertebral block ITP block Superficial PIP block DeepPIP block; PSP block IPP block

BP:brachial plexus; ESP: Erector spinae plane; IPACK: Infiltration between the popliteal artery and capsule of the knee; IPP: Interpectoral plane;ITP: Intertransverse process; PENG: Pericapsular Nerve Group; PIP: parasternal intercostal plane; PSP: Pectoserratus plane; QLB: quadratus lumborum block; SAP: serratus anterior plane; TAP:Transversus abdominis plane; TFP: Transversalis fascia plane.

The regional anesthesia techniques will be categorized using the most recent nomenclature proposed by the European Society of Regional Anesthesia (ESRA) [6–7] as shown in Table 1

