### Intraoperative time

- Demographics: age (years), sex (male/female), BMI (kg/cm^2^).- Medical history: relevant comorbidities (i.e., arterial hypertension, diabetes mellitus, peripheral neuropathy, central neuropathy).- Medication history: with particular attention to anticoagulant and antiplatelet agents, including type and dosage.- Intraoperative data:pre-procedural sedation (i.e., type of drug), and, if sedation was performed, the level of sedation at the time of block execution — assessed using the Richmond Agitation Sedation Scale (RASS) scaletype of regional anesthesiaNeedle used (sharp vs not-sharp and diameter in gauge)use of ultrasound (yes/no, visualization of structures yes/no, in-plane or out-of-plane approach, nerve swelling on injection yes/no)use of a nerve stimulation device (maximum and minimum intensity used)use of a pressure limitertype of local anesthetic used (volume and dose in mg)single local anesthetic drug or mixture of local anesthetic drugsuse of adjuvants (type and dosage in mg or mcg)pain on injection (yes/no)presence (yes/no) of complications, such as hematoma (yes/no) and nerve deficits (yes/no), and their characteristics (sensory – dysesthesia, anesthesia, paresthesia –, or motor deficits in the affected area) at 24 and 48 hours.

As nerve deficits may not be immediately apparent and can be masked by factors such as local edema or limb immobilization [7]. Therefore, sensory and motor deficits will be investigated at 15 and 30 days through a standardized telephone questionnaire aimed at assessing sensory loss, motor impairment, and neuropathic pain (see S2 File). Patients who report the presence of sensory or motor neurological deficits will be referred for management according to the practices of the participating center. For research purposes, they will receive a telephone call every 30 days to monitor the evolution of the deficit until resolution, with a maximum follow-up period of one year.

In summary, the evaluation of complications will require patient contact (either through in-person visits or telephone contact if discharged) at 24 and 48 hours, as well as 15 and 30 days. In the event of nerve complications, the treatment of the lesion will follow the hospital’s local protocol. For the study, follow-up will continue every 30 days until the deficit resolves, or for a maximum of one year from its onset. A timeline is available as Fig 1.

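### The hematoma definition has no attribution term, so a treated surgical hematoma at an overlapping block site can count as a block complication in the primary composite

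*Protocol article*

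**What the plan says.** Under Definitions, the protocol article states the rule in full: "Hematoma: A blood collection at the regional anesthesia site requiring medical and/or surgical intervention".

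The other three components are defined in the same place:

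- Systemic toxicity is an alteration "occurring after regional anesthesia, attributable to systemic absorption of local anesthetic and requiring treatment".
- Nerve injury is "The onset of dysesthesia, anesthesia, or prolonged motor deficit not explained by the pharmacokinetics of the anesthetic used", within an area that fits the block performed.
- Pneumothorax must be "on the same side as the regional anesthesia, confirmed by ultrasound, chest X-ray, or chest CT scan".

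Under Study design and objectives, all four feed the primary endpoint, with procedures as the denominator: "This composite outcome will include nerve injury, hematoma, pneumothorax, and LAST, calculated as the total number of complication events divided by the total number of". That section also makes the incidence of each complication, by type of technique, a secondary objective. The block list in Table 1 includes "Rectus sheath block Ilioinguinal iliohypogastric nerves block TA block Midaxillary TAP block", and also interpectoral, pectoserratus and parasternal blocks.

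Under Intraoperative time, the data items include "presence (yes/no) of complications, such as hematoma (yes/no) and nerve deficits (yes/no"). The characteristics spelled out after that are sensory and motor deficits. The variables listed in the article do not include type or site of surgery.

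**The concern.** Several blocks in Table 1 are placed in, or close to, tissue that the surgeon will also open. A patient may have a rectus sheath block for a midline laparotomy and then need an abdominal wall hematoma drained at that site. Another may have an interpectoral block for breast surgery and then need a wound-bed hematoma evacuated. Each has a blood collection at the block site that required intervention, so each meets the rule as written even if the bleeding was purely surgical.

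Three results are exposed:

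- **Primary composite.** Surgical bleeding can be counted as a complication of the block.
- **Technique-specific incidences.** Any excess would fall on blocks whose site overlaps the operative field.
- **Risk-factor analysis.** The Introduction hypothesizes that anticoagulant use contributes to complications. If anticoagulated patients also bleed more at the surgical site, misattributed surgical hematomas push that odds ratio upward.

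This is misclassification, so more enrolment does not remove it. The rule also lets two centers classify the same patient differently while both follow the protocol, and 43 centers had joined at submission.

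**Working it through.** **Step 1. Compare the four definitions.**

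| Component | Timing term | Cause or exclusion term |
|---|---|---|
| Systemic toxicity | After the block | Attributable to the local anesthetic |
| Nerve injury | Onset | Not explained by pharmacokinetics; matching distribution |
| Pneumothorax | None | None (same side, imaging-confirmed) |
| Hematoma | None | None (at the site, requiring intervention) |

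**Step 2. Look for a cause test elsewhere.** The primary objective reads "The primary objective of the NEURAL study is to determine the overall incidence of complications following regional anesthesia, expressed as a composite outcome". This gives a temporal order but no test of cause. Inclusion and exclusion criteria deals with attribution, but only between two blocks in one patient. The article describes no adjudication of block against surgery.

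**Step 3. The plan's own figures.** Sample size calculation gives an incidence of 0.005 and a minimum of 3,396 subjects. Taking one procedure per subject:

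Expected events = 0.005 × 3,396 = 16.98, about 17.

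The Agresti-Coull 95% interval at this size uses n′ = n + z² and p′ = (np + z²/2)/n′, with total width 2z√[p′(1 − p′)/n′]. With n = 3,396, p = 0.005 and z = 1.96, n′ = 3,399.84 and p′ = 0.00556. The width is 0.0050, a half-width of about 0.25 percentage points. The article states a width of 0.003, for which the same method needs 8,853 subjects. That discrepancy is a separate matter. The relative rises below do not depend on n.

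**Step 4. Sensitivity of the composite.** Let h be the rate, over all procedures, of treated non-block hematomas recorded at the block site. The documents give no value, so every h below is an assumption.

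Extra events = 3,396 × h. Composite = 0.005 + h. Share of events not due to the block = h/(0.005 + h).

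| Assumed h | Extra events | Composite | Relative rise | Share not due to the block |
|---|---|---|---|---|
| 0.05% | 1.7 | 0.55% | 10% | 9% |
| 0.1% | 3.4 | 0.60% | 20% | 17% |
| 0.25% | 8.5 | 0.75% | 50% | 33% |
| 0.5% | 17.0 | 1.0% | 100% | 50% |

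An h of 0.25 percentage points would about equal the half-width in step 3.

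**The case against.** The strongest reply is that counting every treated collection at the site, without judging cause, is a legitimate surveillance choice. It stops local investigators from relabelling block complications as surgical. Pneumothorax has no attribution term either, and nerve injury excludes only a pharmacokinetic explanation. The article also says, under Strengths and limitations, that the study cannot establish causation. Such a choice would be defensible if stated. The article does not state it, and it uses an explicit attribution test for systemic toxicity. It also excludes patients with overlapping blocks because their complications could not be assigned to one block. The looseness of the pneumothorax wording does not repair the hematoma wording.

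Other limits on the point do stand:

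- A reader might infer that surgical hematomas will enter the composite as a matter of course. The text supports only that they can: a collection must lie at the block site and need intervention, so bleeding elsewhere in the wound does not count.
- A reader might add a pre-existing fracture hematoma under a hip block. The objective speaks of complications that follow the block, which largely disposes of that case.
- A reader might conclude that the case report form cannot separate the sources afterwards. The item list is introduced as examples, and neither the form nor the full protocol is shown, so this cannot be claimed.
- A reader might see a distorted comparison between regions. The article plans incidences and risk factors for each group and states no between-region comparison as an objective.

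**Conclusion.** The concern holds as a defect in a stated rule. Followed literally, the definition lets a treated postoperative surgical-bed hematoma at an overlapping block site count in the primary composite and in the technique-specific incidences. The direction is upward for the incidence. It is also upward for the anticoagulant association, on the assumption that anticoagulation raises surgical-site bleeding regardless of the block.

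The size is unknown. What follows from the plan's own figures is the sensitivity: with about 17 expected events, each 0.1 percentage point of non-block hematoma adds about 3.4 events, one fifth of the expected total. A reader might go further and multiply an assumed share of blocks in the operative field by an assumed surgical hematoma rate, to reach a specific inflation factor. The documents support neither input, so no such factor should be quoted.

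**What to change.** Keep the present site-based wording as the rule for capturing cases, and add that the collection must be first present after the block. Add one field to the hematoma item for likely source: block, surgery or trauma, or indeterminate. Count block-attributed and indeterminate cases in the primary composite, and report a sensitivity analysis that counts every captured collection at the site.

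Surgical collections should not be excluded in the definition itself. They would then never be recorded, the surgery-or-trauma category would stay empty, and the sensitivity analysis could not be run.

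The cost is one clause and one REDCap field, completed only for patients with a hematoma. The article says the study had not started at submission, and the source is best recorded prospectively. The downsides are some local investigator judgement, which the sensitivity analysis bounds, and a possibly lower reported hematoma rate.

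### The pneumothorax definition counts any same-side air on imaging, so air from chest surgery or trauma can enter the primary composite and could not be separated later on the listed data

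*Protocol article*

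**What the plan says.** The Definitions section gives four components of the composite.

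- Pneumothorax: "The presence of an air crescent consistent with pneumothorax on the same side as the regional anesthesia", with confirmation on ultrasound, X-ray or CT.
- LAST: an alteration arising after the block, "attributable to systemic absorption of local anesthetic and requiring treatment".
- Hematoma: "A blood collection at the regional anesthesia site requiring medical and/or surgical intervention".
- Nerve injury: new sensory disturbance or prolonged motor deficit "not explained by the pharmacokinetics of the anesthetic used, within the distribution area consistent with the performed block".

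Study design and objectives places all four in the primary outcome, "calculated as the total number of complication events divided by the total number of procedures". It also asks for the incidence of each complication by block family.

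The fascial column of Table 1 lists chest-wall techniques, for example "Rhomboid intercostal plane block Retrolaminar block", along with paravertebral, ESP, SAP, ITP and parasternal blocks. Inclusion and exclusion criteria admit every consenting adult with an eligible single-shot block. They exclude only patients unable to consent and those with multiple blocks that overlap. Patients with paravertebral and ESP blocks of the chest are discussed there as possible participants.

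**The concern.** Laterality is the only link between the air and the block. An operation or injury that opens the pleura on the blocked side leaves air on that same side, so laterality does not separate the causes.

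The plan recognises this kind of problem elsewhere. It excludes a paravertebral and an ESP block on the same side of the chest because a pneumothorax could not be assigned to one of them. A block combined with same-side pleural surgery raises the same difficulty and is admitted.

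Three results are exposed: the primary composite, the pneumothorax incidence for fascial plane blocks, and any risk-factor model in which chest surgery travels with the type of block. The error can only raise the incidence. That is also the direction of the hypothesis in the Introduction, that true incidence exceeds registry figures. A larger sample would not remove it.

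**Working it through.** **Step 1. Compare the definitions.**

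| Component | Onset after block | Link to block | Other cause ruled out | Severity or treatment |
|---|---|---|---|---|
| LAST | yes | attributable to the drug | by attribution | treatment |
| Hematoma | not stated | at block site | no | intervention |
| Nerve injury | onset required | block's distribution | pharmacokinetics only | none |
| Pneumothorax | not stated | same side | no | none |

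Pneumothorax has the loosest link to the block, but it is not the only component with gaps. Nerve injury also lacks a severity clause and does not rule out surgical injury.

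**Step 2. Could the cases be removed afterwards?** The data listed under Intraoperative time cover demographics, comorbidities, medication, sedation, block technique, drugs and complications. Type and side of surgery, chest trauma, prior chest air and chest drain are not listed. On these fields the answer is no.

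**Step 3. The plan's own figures.** Sample size calculation gives an incidence of 0.005, a 95% interval of total width 0.003 and n = 3,396. Solving for n at width 0.003 gives 8,676 (Wilson) or 8,853 (Agresti-Coull), so 3,396 is not reproduced. At width 0.005, Agresti-Coull gives 3,395. That mismatch is a separate matter and does not bear on this point. I take n = 3,396 as stated, with one procedure per subject.

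Expected events: 3,396 × 0.005 = 16.98, about 17.

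**Step 4. Effect of added events.** Let s be the share of patients whose surgery or injury opens the same-side pleura, and q the proportion of those with same-side air on imaging. Neither is in the documents. I assume s = 1%, 3%, 5% and q = 5%, 10%, 20%.

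Added events = 3,396 × s × q. Composite = 0.005 + s × q.

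| s | q = 5% | q = 10% | q = 20% |
|---|---|---|---|
| 1% | 1.7 (0.55%) | 3.4 (0.60%) | 6.8 (0.70%) |
| 3% | 5.1 (0.65%) | 10.2 (0.80%) | 20.4 (1.10%) |
| 5% | 8.5 (0.75%) | 17.0 (1.00%) | 34.0 (1.50%) |

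In the middle cell, 10.2 / (16.98 + 10.2) = 38% of counted events would not be due to the block. The shift of 0.003 equals the whole stated interval width. It is 60% of the width that n = 3,396 delivers under Agresti-Coull (0.003 / 0.005). The composite doubles when s × q = 0.5%, for example 5% × 10%.

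**Step 5. Fascial plane blocks.** If the exposed patients all fall in this family and it makes up a fraction f of procedures, the added incidence there is s × q / f. This exceeds s × q for any f below 1. The documents do not give f.

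**The case against.** The strongest reply is that the definition should be read in its setting. The section defines complications, and the objective concerns complications that follow regional anesthesia. Air known before the block does not fit that description, so the case for pre-existing air is the weakest part. This reply does not cover surgical air, which also appears after the block. The Strengths and limitations section mentions training and standardized definitions across centers, and the full approved protocol (S3 File, not shown) may hold further guidance or fields. That cannot be confirmed. The article nevertheless states its operative definition and criteria, and the objection is to what they say.

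The size is wholly assumed, including how often these patients are imaged. Five of the nine cells above leave the composite at 0.75% or below, and the lowest adds fewer than two events. A reader might infer that false events will outnumber true ones. Within the grid this happens only when a 20% air rate is paired with a share of 3% or more, and nothing in the documents supports choosing those cells.

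The random-intercept models planned for center-level clustering would absorb part of the difference in imaging habits in the risk-factor analyses. They do not correct the crude incidence.

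A reader might also infer that only symptomatic or treated pneumothorax should count, to match hematoma and LAST. The documents do not support this as a correction. Nerve injury has no severity threshold either, and the restriction would remove genuine, imaging-confirmed block injuries and so change the estimand. Attribution can be repaired without it.

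**Conclusion.** The concern holds as a defect in a stated rule. Applied literally, the definition counts surgical or traumatic air on the blocked side as a block complication, eligibility lets such patients in, and the listed data would not identify them. The text does not show that such events will certainly be counted, since investigators may use judgement. Unguided judgement across 43 or more centers would, however, undercut the standardization that the article claims.

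The mechanism is clear from the document, but its size is not. Under assumed shares of 1% to 5% and air rates of 5% to 20%, about 2 to 34 events join about 17 expected, moving a true 0.5% to between 0.55% and 1.50%. With so few expected events, even the middle of that range is material to the primary estimate.

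**What to change.** 1. Define pneumothorax as same-side air on imaging that is new after the block and not explained by surgery, chest trauma, a chest drain or pre-existing air.
2. Add REDCap fields for same-side pleural breach (surgery or trauma) and for air present before the block.
3. Treat patients with a same-side pleural breach as not assessable for the pneumothorax component, unless new air was documented after the block and before incision.
4. Keep these patients in the composite denominator for the other three components, and report the composite with and without them as a sensitivity analysis.
5. Record whether each pneumothorax was symptomatic, treated or incidental, and report this descriptively. Do not restrict the primary composite on this basis.

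The cost is one clause, one assessability rule and a few form fields. The article says that the study had not started at submission. If recruitment has since begun, an amendment is needed, with the new fields completed for patients already enrolled where records allow. The downside is small: some true block-related pneumothoraces in patients with a pleural breach will go uncounted, so the composite that includes these patients is slightly conservative for this component.
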